According to our protocol enteral nutrition will start after the 72^nd^ hour of life as minimal enteral feeding (MEF), intake less than 20 mL/Kg/day of enteral feeding will be administered. The increase will be by 20 mL/Kg/day if enteral nutrition is well tolerated. All the infants, according to our standardized protocol, will start parenteral nutrition on the first day of life. The infants will be fed with human milk, if available, (human milk will be fortified at an achievement of an enteral intake of 100 ml/Kg/d), or with a preterm formula (75–80 Kcal/100 mL). The nutrition will be administered via the nasogastric route.

On the randomization day intestinal and cerebral regional oximetry will be measured via near infrared spectroscopy (NIRS) (INVOS- 5100 C) sensors placed over the abdomen (splanchnic bed) and on the forehead (cerebral bed). Recording of the tissues oximetry will start 30 minutes before the feed and will stop 30 minutes after the end of the nutrition. Intestinal and celebral oximetry will be measured before the feed (B_0_) and 30 minutes after the feed (B_1_) by bolus; during the continuous nutrition the measurements will be performed before (C_0_), 30 minutes from the start of the nutrition (C_1_) and 30 minutes after the end of the gavage (C_2_).

The TOI will be obtained simultaneously at the two locations. The TOI measurement recordings will be obtained for 3 minutes from both the head and the abdomen. Those measurements will be combined as a ratio of abdominal TOI over brain TOI to produce a CSOR (TOI_abdomen_/TOI_brain_). Arterial haemoglobin oxygen saturation, measured by pulse oximetry, will be recorded during the NIRS tracing. NIRS tracing will be used only in the absence of desaturation (< 85% arterial saturation).

Capillar haemoglobin concentration will be measured on the day of the evaluation.

An evaluation of blood flow velocity of the superior mesenteric artery (peak sistolic and end-diastolic velocity, mean velocity, and pulsatility index) will be performed meanwhile. To achieve imaging of the SMA the transducer will be placed on the mid-abdomen above the umbilicus. The SMA will be identified at its emergency from the aorta and sample volume will be placed a few millimetres from its origin. Neonatologists with the same expertise and manual ability will perform the ecocholordoppler evaluations. The evaluations and the measurements will be performed on 5 contiguous homogeneous waves.

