Measurements of body weight, length and head circumference will be performed at predefined times: at birth, at the beginning of MEF, on the randomization day, at the achievement of full enteral feeding, at 28 days of life and at 36 weeks of gestational age.

Parameters of feeding tolerance are those routinary used in the NICU (maximum gastric residual and residual appearance). The enteral nutrition will be discontinued or carried on according to our feeding protocol.

The follow-up will end at the achievement of a full enteral feeding, enteral intake of 160 mL/Kg/die or at 28 days of life, whichever occurs later. Patients may drop-out before this intended end because of the following withdrawal causes:

Withdrawal of the consent by the relatives

Severe skin reaction due to the skin probe

Transferral to another hospital

Death

After study end, patients will be fed according to the standard protocol of our Unit.

During the study, recommended diagnostic and therapeutic procedures are those usually performed as standard care in our Unit.

No new special measure for safety is planned since all the diagnostic and therapeutic procedures are part of the standard approach to the VLBW infant in our Unit.

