### Statistical considerations

#### Randomization

Randomized interventions are described in Section ‘Methods and Design’. This section summarizes procedures and methodology, which will be adopted**.**

Patients eligible to randomization: all VLBW infants enrolled and eligible to the study, either IUGR or non-IUGR, who fulfil the following requirements:

1. achievement of 100 mL/kg/day of enteral nutrition;

2. adequate ventilation i.e. infants who are not intubated and not in-cPAP with a FiO2≥50% at the achievement of 100 mL/Kg/day of enteral nutrition;

3. no NEC;

4. Informed consent from parents or guardians.

When to randomize:

a. * After *achievement of 100 mL/kg/day of enteral nutrition in presence of adequate ventilation (see point 2 above)

Modalities of randomization:

b. Logistics: investigators will ask for randomization by access to a specific software which will provide the assigned arm, after check on the eligibility criteria.

c. Methodology: randomization will be stratified (IUGR vs non-IUGR) and by blocks: the random assignment will be produced by an automatic procedure Ranlist [19] and will be based on random permuted blocks of small size, given the limited number of infants expected in each stratum.

**Randomization refusals:** if parents or guardians do not agree with randomization, patients will be excluded from the study and should be fed according to nutrition procedure regarded as the most appropriate for the child based on the Unit standard policy.

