#### Statistical analysis

The primary aim of the study is to compare the impact on intestinal perfusion of 2 different nutrition modalities, bolus (BN, Group A) versus a 3-hour nasogastric nutrition (CN, Group B). The impact on intestinal perfusion is defined as the difference between pre- and post-prandial CSOR values measured with NIRS 30 minutes before feeding and at the expected peak after feeding (3 hours in CN and 30 minutes in BN). Pre- and post-prandial CSOR values will be calculated as the mean of 5-minute NIRS evaluations about the intended time-point (e.g. for baseline CSOR measurement, 2.5 minutes before and 2.5 minutes after the 30th minute before start of the randomized feed). Given that the study is a cross-over study, each infant will be evaluated both for CN and BN and the cross-over CSOR difference will be the primary endpoint.

As a secondary analysis, the cross-over difference of CSOR values as well as that of SO2s values (i.e. the splanchnic saturation slope) will be analysed comparing intra-uterine growth (IUGR vs. non-IUGR).

The impact of the 2 nutrition modalities on CSOR will also be studied in a multivariable context, adjusting for factors including the baseline CSOR value, the baseline Doppler flow velocimetry (both measured within the first 72 hours of life) and the intra-uterine growth (IUGR vs. non-IUGR).

Other secondary analyses include:

· Comparison of the time needed to reach full enteral feeding (i.e. days from randomization till enteral intake of 160 mL/Kg/day of formula or human milk) by randomized arm;

· Comparison of growth as measured by weight, length and head circumference by randomized arm. Main comparison will be between measures at randomization and at achievement of full enteral feeding. The growth at 28 days of life will also be compared with the appropriate standard growth curves.

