The primary end-point analysis as well as all secondary analyses regarding randomized patients will be based on the ITT (intention-to-treat) principle. Comparisons of the two arms accounting for deviations from the assigned arm (analyses by “performed treatment”) will also be added to this main analysis. The primary endpoint will be analyzed with a two-tailed matched pairs t-test, after checking of appropriateness of assumptions. In particular, checking will concern the normality assumption, since period effect and cross-over effect appear both very unlikely in this study. Should normality be not adequate, non-parametric test such as the Wilcoxon signed ranks test will be applied [20]. An appropriate generalized linear model will be used to investigate the relationship between the CSOR cross-over difference and the candidate covariates. Should any raw CSOR observations be missing (e.g. NIRS instrument failed to measure or to save measurements), their estimation via imputation or other appropriate methods will be taken into account. The comparison of growth variables by randomized arm will be performed with either the two-tailed t-test or a non-parametric alternative (e.g. Mann–Whitney test), should the normality assumption be not reasonable. The time from randomization till achievement of the full enteral feeding will be analysed with the Kaplan-Meier estimator, in which full enteral feeding as defined in the protocol will be considered as the sole ‘event’, while censoring will occur for withdrawal for any cause. Standard errors will be computed according to Greenwood formula and the log-rank test will be used for univariate comparisons.

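### Time to full enteral feeding: death is censored like any other withdrawal, so one minus Kaplan-Meier overstates the proportion fed if an infant dies while others go on to reach full feeding

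*Protocol article*

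**What the plan says.** The Statistical analysis section lists, among the secondary analyses by randomized arm, "Comparison of the time needed to reach full enteral feeding", counted in days from randomization to an intake of 160 mL/kg/day. It then fixes the method: "The time from randomization till achievement of the full enteral feeding will be analysed with the Kaplan-Meier estimator". Full feeding is the only event, and "censoring will occur for withdrawal for any cause". For precision and testing: "Standard errors will be computed according to Greenwood formula and the log-rank test will be used for univariate comparisons".

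What counts as withdrawal is set out in the follow-up text under Methods and design (Stratification subsection): "Patients may drop-out before this intended end because of the following withdrawal causes". Four causes follow: withdrawal of consent, severe skin reaction to the probe, transfer to another hospital, and death. Follow-up ends at full feeding or at 28 days of life, whichever is later.

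The article names no competing-risk method, composite endpoint or sensitivity analysis for death.

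**The concern.** Kaplan-Meier treats a censored infant as someone whose later chance of the event is the same as that of the infants still under observation. For a transferred infant this is a working assumption. For an infant who has died it is false, because the chance of reaching 160 mL/kg/day is then zero. Death is a competing event, and censoring it removes the infant from the denominator instead of counting a failure to reach full feeding.

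The follow-up rule makes this more visible. Because follow-up continues until full feeding if that comes after day 28, there is no planned administrative censoring before the event. Each infant either reaches full feeding or is withdrawn. An arm's curve therefore ends at 100% unless its longest observed time is a withdrawal. At stake is how the curves are read: two arms with different numbers of deaths could both appear to reach complete feeding success.

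**Working it through.** **Inputs from the article.** About 20 infants, 10 per group (Methods and design; Sample size). The clock starts after "achievement of 100 mL/kg/day of enteral nutrition in presence of adequate ventilation". On feed advancement: "The increase will be by 20 mL/Kg/day if enteral nutrition is well tolerated". The shortest path to full feeding is therefore (160 − 100)/20 = 3 days.

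**Assumptions.** The article gives neither mortality nor the distribution of feeding times. The numbers and times below are illustrative.

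**The plan's own figures.** The article states none for this endpoint. Its only power figures (Table 1: 84%, 80%, 78%) concern the primary CSOR difference. A two-sided paired t-test with n = 20 gives 84.4%, 80.7% and 78.7%, so they reproduce, and nothing here touches them.

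**Formulas.** At each time t_j let n_j be the number at risk, d_j the number reaching full feeding and m_j the number dying.
- Kaplan-Meier with deaths censored: S(t) = ∏(1 − d_j/n_j), and the apparent proportion fed is 1 − S(t).
- Aalen-Johansen: F(t) = Σ O(t_j−)·d_j/n_j, where O is the product of 1 − (d_j + m_j)/n_j over earlier times. With no other censoring, the final F is simply the number fed divided by the number randomized.

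**Step 1: deaths before the last event (arm of 10).**
- One death at day 4.5, nine infants fully fed on days 3 to 11, one per day. After days 3 and 4, S = 9/10 × 8/9 = 8/10. The death leaves seven at risk, and all seven are later fed, so S = 0. 1 − S = 100%; F = 9/10 = 90%.
- Two deaths at day 4.5, eight infants fed on days 3 to 10. S = 8/10 after day 4, then six at risk and six events, so S = 0. 1 − S = 100%; F = 8/10 = 80%.

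**Step 2: deaths after the last event.**
- One death at day 12, nine fed on days 3 to 11: S = 9/10 × 8/9 × … × 1/2 = 1/10. 1 − S = 90%, which is correct.
- Two deaths after eight events: S = 9/10 × 8/9 × … × 2/3 = 2/10. 1 − S = 80%, also correct.
- Mixed case: eight fed on days 3 to 10, one death at day 4.5 and one at day 11. S = 8/10 × (6/7 × 5/6 × … × 1/2) = 8/10 × 1/7 = 0.114. 1 − S = 88.6% against a true 80%.

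**Step 3: a reading during follow-up.** Take feeding times of 3, 3, 4, 4, 5, 5, 6, 7, 8 and 10 days, with the slowest infants replaced by those who die. The true proportion fed by day 5 is 6/10 = 60% in every row.

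| Deaths | Day of death | 1 − S at day 5 |
|---|---|---|
| 1 | 1.5 | 1 − 3/9 = 66.7% |
| 1 | 3.5 | 1 − 8/10 × 3/7 = 65.7% |
| 2 | 1.5 | 1 − 2/8 = 75.0% |
| 2 | 3.5 | 1 − 8/10 × 2/6 = 73.3% |
| 1 or 2 | 5.5 | 60% (no effect yet) |

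**Step 4: a range under constant hazards.** With feeding hazard a and death hazard b per day, 1 − S = 1 − exp(−aT) and F = a/(a + b) × [1 − exp(−(a + b)T)]. For mean feeding times of 3 or 6 days and b from 0.002 to 0.02, the excess at T = 14 days runs from 0.6 points (99.1% against 98.5%) to 7.6 points (90.3% against 82.7%).

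**The case against.** The best case for the plan has four parts.

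1. **Few or no deaths may fall in the window.** Randomized infants already take 100 mL/kg/day, have no NEC and meet the ventilation criterion, and a tolerant infant needs only about three more days. This stands: with no such death the two estimates are identical.
2. **The bias depends on timing.** A reader might infer that any death drives the curve to 100%, so that an arm with more deaths always looks fully successful. Step 2 shows otherwise: deaths after the last event leave the final estimate correct. A reader might also assume that infants who die are mainly those who tolerate feeds poorly. The article links growth restriction to intolerance and NEC, but says nothing about who dies after randomization. If deaths did fall among slow feeders with long at-risk times, they would tend to come late, where this bias is smallest.
3. **The planned test is not invalid.** The log-rank test with deaths censored is a legitimate comparison of cause-specific hazards. What fails is reading the curve as the probability of reaching full feeding. The article does not announce a final proportion fed, and the publication is to include safety analyses, where deaths would be expected to appear.
4. **The endpoint is secondary** in a study that calls itself explorative.

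All four limit the size of the point. None removes it: the censoring rule is stated, it covers death, and nothing elsewhere in the article corrects it.

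**Conclusion.** The point holds in a limited form. Read together, the two sections censor death before full feeding, and one minus Kaplan-Meier then overstates the proportion reaching 160 mL/kg/day whenever an infant dies while others still at risk later reach it. In an arm of 10 where all survivors are fully fed, the final overstatement is 10 points for one death and 20 for two, provided the deaths precede the last event. It is zero with no deaths or with deaths only after the last event. These sizes rest on assumed death counts and feeding times, since the article supplies neither.

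The documents do not support the wider conclusions that the log-rank comparison is wrong, that deaths are tied to feeding intolerance, or that the primary CSOR analysis or its power is affected. This is a minor but worthwhile correction.

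**What to change.** Replace the censoring rule for this endpoint with wording along these lines: death before full enteral feeding is a competing event; the Aalen-Johansen cumulative incidence of full enteral feeding is reported by arm, with Gray's test if a test on that scale is wanted; the log-rank test is kept and labelled as the comparison of cause-specific hazards; deaths are reported by arm; infants withdrawn for consent, transfer or severe skin reaction are censored.

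All three non-fatal causes should be named, so that every listed withdrawal cause has a rule. Simply leaving infants who died in the risk set as never fed is not an exact substitute for Gray's test when others are censored at random, because weighting is then needed.

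The cost is one sentence and a standard routine. No new data are required, and the sample size and primary analysis do not change.

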### Aims of the study

Primary aim of this study:

1. To evaluate the changes in the intestinal perfusion and oximetry determined by feeding in VLBW infants fed by 3 hours nasogastric nutrition (CN) *versus* infants fed by bolus nutrition (BN).

Secondary aims of the study:

2. To compare if changes in the intestinal perfusion and oximetry induced by feeding are different between IUGR and NON-IUGR infants.

3. To compare growth and nutritional status of the 2 groups by randomized arm.

4. To test if changes in intestinal oximetry and perfusion can be reliable predictors of feeding intolerance (days necessary to achieve full enteral feeding)*.*

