### Endpoints

The endpoint for the primary aim will be the cross-over difference of CSOR values, measured with NIRS before and at the end of the randomized feeds.

Aims 1 to 4 will be pursued analysing the following endpoints:

· The cross-over difference of CSOR values and of rSO2s values (i.e. the splanchnic saturation slope) in IUGR and non-IUGR infants.

· Growth and nutritional status will be measured by weight, length and head circumference. Main comparison will be between measures at randomization and at achievement of full enteral feeding. The growth at 28 days of life and at 36 weeks of gestational age will also be compared with the appropriate standard growth curves.

· The difference in the CSOR values pre- and post- feeding will be compared with the baseline CSOR value and the baseline Doppler flow velocimetry (both measured within the first 72 hours of life)*.*

· Comparison of the time needed to reach full enteral feeding (i.e. days from randomization till enteral intake of 160 ml/kg/day of formula or fortified human milk) by randomized arm;

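### Aim 4, whether changes in oximetry and perfusion predict days to full enteral feeding, has no matching endpoint or analysis

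*Protocol article*

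**What the plan says.** Aims of the study lists as aim 4: "To test if changes in intestinal oximetry and perfusion can be reliable predictors of feeding intolerance (days necessary to achieve full enteral feeding". The Endpoints section then states "Aims 1 to 4 will be pursued analysing the following endpoints". Two items in that list come near aim 4:

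- For the CSOR response: "The difference in the CSOR values pre- and post- feeding will be compared with the baseline CSOR value and the baseline Doppler flow velocimetry".
- For feeding: "Comparison of the time needed to reach full enteral feeding", by randomised arm.

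Statistical analysis repeats the feeding item as "days from randomization till enteral intake of 160 mL/Kg/day of formula or human milk) by randomized arm". It analyses this time with Kaplan-Meier and adds that "the log-rank test will be used for univariate comparisons". Full feeding is the only event, and "censoring will occur for withdrawal for any cause". The list of withdrawal causes in Methods and design includes death and transfer to another hospital.

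The same section describes one regression, a generalised linear model relating the CSOR cross-over difference to candidate covariates. The factors named are baseline CSOR, baseline Doppler and IUGR status. Randomisation is stratified by IUGR, with about 10 infants in each stratum.

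**The concern.** Aim 4 is about individual infants: does an infant whose splanchnic oxygenation or SMA flow responds differently to a feed take longer to reach full feeding? A by-arm comparison asks something else, namely whether the regimen given after the cross-over day changes that time. Two arms could have identical curves while the CSOR response predicts strongly within each, or the reverse.

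If the plan is followed as written, a stated secondary aim yields no result. If an analysis is added later, the predictor, any cut-off and the adjustment would be chosen after the data from about 20 infants have been seen. The Discussion makes the gap more visible, because it suggests that poor perfusion may lengthen the time to full feeding.

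Two side issues concern the by-arm analysis itself. The randomisation stratum is not mentioned in the test. Deaths are censored, although an infant who dies cannot go on to reach full feeding.

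**Working it through.** **1. Aim against analysis.** Aim 4 needs an oximetry or perfusion change as predictor and time to full feeding as outcome.

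| Place | Outcome | Compared with or explained by |
|---|---|---|
| Endpoints, CSOR item | pre-post CSOR difference | baseline CSOR, baseline Doppler |
| Endpoints, feeding item | time to full feeding | randomised arm |
| Statistical analysis, feeding item | time to full feeding | randomised arm |
| Statistical analysis, regression | CSOR cross-over difference | baseline CSOR, baseline Doppler, IUGR and other candidate covariates |

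No row has the pairing that aim 4 requires. The remaining endpoints (cross-over difference by IUGR status, growth) do not involve time to full feeding as an outcome.

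**2. The plan's own power figures.** Table 1 concerns the primary endpoint only. Exact two-sided paired t-test power, with n = 20, 19 degrees of freedom and noncentrality (difference/SD) × √20, gives:

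- 0.07 with SD 0.10: 84.4% (stated 84%)
- 0.10 with SD 0.15: 80.7% (stated 80%)
- 0.13 with SD 0.20: 78.7% (stated 78%)

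The table reproduces. It says nothing about aim 4, for which no figure is given.

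**3. What about 20 infants could show for aim 4.** These are illustrations at two-sided alpha 0.05. The event counts of 20, 18 and 16 are assumptions.

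Cox model with a continuous predictor: detectable HR per SD = exp[(1.960 + 0.842)/√D].

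- D = 20: exp(2.802/4.472) = 1.87
- D = 18: exp(2.802/4.243) = 1.94
- D = 16: exp(2.802/4.000) = 2.01

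At HR 1.5 per SD the power is 44%, 41% and 37% respectively.

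For comparison, the planned by-arm log-rank: detectable HR = exp[2.802/√(D/4)], giving 3.50, 3.75 and 4.06. At HR 2 its power is 34%, 31% and 28%.

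**4. Tied times.** Methods and design raises feeds by 20 mL/kg/day when tolerated. From the randomisation threshold to full feeding takes (160 − 100)/20 = 3 days if all goes well. Times counted in days will therefore often coincide.

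**5. Censoring.** Follow-up runs to full feeding or day 28, whichever is later, so the stated plan censors only withdrawals. Kaplan-Meier treats a censored infant as still able to reach full feeding. Suppose, purely to show the mechanism, that one of 10 infants in an arm dies first and the other nine all reach full feeding. Kaplan-Meier then ends at 100%, whereas the proportion that reached it is 9/10 = 90%. The documents give no death rate, so this does not estimate the size of any bias.

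**The case against.** The strongest reply is that this is a condensed article of a study that calls itself explorative, and that its wording is open. The other secondary analyses are said to include those listed, and the factors in the univariate comparisons are not named. A log-rank test by grouped CSOR change is therefore not strictly excluded, and model detail for a last secondary aim often sits in a fuller document. Part of this stands: one cannot say that no such analysis will ever be done. It does not remove the mismatch, because the Endpoints section claims that its list covers all four aims and the list does not. A grouped log-rank would also need a cut-off, and none is given.

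Several stronger readings are tempting but unsupported.

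- **That aim 4 goes untested because of how the log-rank test or the censoring is specified.** Changing either would leave aim 4 where it is.
- **That the planned regression is aim 4 reversed.** Time to full feeding is not named anywhere in that model. It answers a different question.
- **That the by-arm log-rank is invalid or favours one arm.** With deaths censored it still tests the cause-specific hazard, and nothing in the documents shows deaths differing by arm. Exposure is also short when feeds are tolerated.
- **That transfers are mishandled.** Censoring them is conventional.
- **That the test is stated to be unstratified.** This is inferred from the word univariate and from the absence of any stratified test. The Discussion says only that IUGR infants may take longer.

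**Conclusion.** The point holds as a mismatch between a stated aim and the stated endpoints and analyses. One of four aims has no analysis that could answer it. This rests on the text alone and needs no assumption about effect sizes. The primary endpoint and its power are untouched.

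The two side points are smaller. Stratifying the arm comparison by IUGR would match the analysis to the randomisation. The censoring rule makes the Kaplan-Meier proportion too high if any infant dies before full feeding, by an amount that the documents do not allow one to estimate.

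The detectable effects above rest on assumed event counts and on approximate formulas that ignore ties and covariate adjustment. They show that an aim 4 analysis would be exploratory, not that it should be omitted.

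**What to change.** **Aim 4.** Prespecify one exploratory Cox model of days from randomisation to full enteral feeding.

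- Predictor: the pre-post CSOR change on the randomisation day, stating whether it is taken from one feed or averaged over both.
- A second, separate model: the change in one SMA Doppler measure, named in advance from those the protocol records.
- Adjust for arm, since the regimens differ after the cross-over; stratify by IUGR; and state the method for tied times (for example Efron).
- Report the hazard ratio with its interval, and label the result exploratory.

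If the sponsor does not want this analysis, reword or withdraw aim 4.

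**By-arm comparison.** Use a log-rank test stratified by IUGR. Show the proportion reaching full feeding as a cumulative incidence with death as a competing event, or count infants who die as not having reached it. Transfers may stay censored.

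**Cost.** A few sentences and some extra analysis of data already planned for collection; no additional infants or measurements. The downside is wide intervals, from about 20 infants and many tied times.

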#### Stratification

Randomization will be stratified in two groups: IUGR infants (approximately 10 children) and NON-IUGR infants (approximately 10 children).

At the achievement of an enteral intake of 100 mL/Kg/day the patients (IUGR and NON IUGR separately) will be randomized in 2 groups: Group A (n=10) will start with bolus administration of nutrition (in 10 minutes); then, after at least 3 hours, they will be fed by the same amount of feed administered as continuous nutrition for 3 hours; Group B (n=10) will start with continuous administration of nutrition for 3 hours followed by a bolus administration of the same amount of feed (in 10 minutes) after at least 3 hours.

The infants of the Group A will be fed with continuous nutrition until the achievement of full enteral feeding (enteral intake of 160 mL/Kg). The infants of the Group B will be fed with 7 or 8 boli/d until the achievement of full enteral feeding.

If, due to clinical instability (i.e. desaturation episodes or bradicardia) during the feeding, a change occurs in the modality of feeding, the results will be analyzed according to the “intention to treat” or the “by treatment” analysis.

All the patients will undergo a baseline evaluation in the first 72 hours of life including: cerebral ultrasound, cardiac ultrasound and abdominal ultrasound.

After birth, in the first 24 hours of life, and in the transitional period, between the 48^th^ and 72^nd^ hours of life, all infants’ intestinal perfusion will be evaluated with NIRS and the echocolordoppler (evaluation of the superior mesenteric artery blood flow) will be performed. The evaluations with NIRS and with the echocolordoppler will be performed under condition of clinical stability (absence of arterial desaturation or instability of cardiocirculatory parameters). Data from NIRS will be collected for 3 hours. Other anamnestic and clinical data will be collected (gestational age, umbilical arterial pH, race, obstetrical anamnesis, mode of delivery, umbilical arterial and venous catheters, patent ductus arteriosus, respiratory distress syndrome, mechanical ventilation, episodes of clinical sepsis). All the infants will be at nothing per os (npo) at the moment of the first two evaluations.

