### Sample size

This single-center study will recruit patients for 2 years (24 months) since official opening. The expected accrual is about 20 VLBW infants, either IUGR or non-IUGR. The power calculations below are based on a two-tailed t-test with I-type error α=0.05 and show the power that the 20-patient study will achieve under various differences in CSOR from the ‘baseline’ impact observed under BN. On the basis of previous studies [21] this is expected to be 0.10 (mean of CSOR pre-post prandial difference), while various hypothesis are made about its standard deviation, σ_CSOR_

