## Discussion

This is an explorative study. Evaluations of intestinal oximetry and superior mesenteric artery blood flow after the feed may help in differentiating how the feeding regimen alters the splanchnic blood flow and oxygenation and if the changes induced by feeding are different in IUGR versus NON IUGR infants.

We postulate that TOI will be altered in the vascular bed when blood flow is decreased; the resultant acidosis in poorly perfused tissues may also further increase the dissociation of oxygen from haemoglobin and increase the portion of reduced haemoglobin detected with NIRS. This condition may be present in IUGR infants and this condition may alter feeding tolerance thus requiring a longer time to achieve full enteral feeding and increasing the episodes of feeding intolerance.

Gut perfusion may depend on the way of administering feeding, bolus or continuous nutrition, so this study may suggest which is the best way to feed VLBW infants.

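### Growth and time to full enteral feeding are compared by arm without the IUGR stratum used in randomization, which costs power to the extent that IUGR affects growth and, for feeding time, only if its effect is strong

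*Protocol article*

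**What the plan says.** Under Randomization, the protocol article states that "randomization will be stratified (IUGR vs non-IUGR) and by blocks", with small permuted blocks. The Stratification section expects roughly 10 infants in each stratum and 10 in each of Groups A and B.

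The Discussion gives a reason to think the stratum matters for feeding. It describes a state of reduced perfusion that may be present in IUGR infants and says that "this condition may alter feeding tolerance thus requiring a longer time to achieve full enteral feeding".

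Under Statistical analysis, two by-arm comparisons are specified:

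- Growth: "The comparison of growth variables by randomized arm will be performed with either the two-tailed t-test or a non-parametric alternative", with Mann–Whitney as the example.
- Days from randomization to full enteral feeding: Kaplan-Meier curves, and "the log-rank test will be used for univariate comparisons".

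No stratified or IUGR-adjusted version is named for either. IUGR is an adjustment factor only in the multivariable model for CSOR.

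**The concern.** Blocking within strata makes the arms nearly equal in their share of IUGR infants, so a difference in outcome between IUGR and non-IUGR infants largely cancels from the arm contrast. A test that ignores the stratum still counts that difference as residual noise. Its standard error is then too large for the design actually used.

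The adjustment is also placed where it helps least. The CSOR contrast is within infant, so an IUGR effect on the CSOR level cancels there anyway. Growth and feeding time are compared between infants, 10 against 10, and that is where the variation between strata stays in the error term. Growth by arm is a stated secondary aim and time to full feeding by arm a listed endpoint. What is at stake is a missed difference in these two comparisons.

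**Working it through.** **The plan's own power figure.** The article gives power only for the primary paired test, a "two-tailed t-test with I-type error α=0.05". With n = 20, 19 degrees of freedom and noncentrality (difference/σ)·√20, the rows of Table 1 give:

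- 0.07/0.10: noncentrality 3.13, power 84.4% (stated 84%)
- 0.10/0.15: noncentrality 2.98, power 80.7% (stated 80%)
- 0.13/0.20: noncentrality 2.91, power 78.7% (stated 78%)

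Table 1 reproduces. It concerns a within-infant difference and does not bear on the two comparisons discussed here, for which no power is stated.

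**Inputs from the article.** About 20 infants, two strata of about 10, 1:1 allocation stratified by IUGR, two-sided 5% level.

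**Assumptions, because the article gives no figures.** Exactly 5 infants per arm in each stratum; an IUGR effect b on growth in within-stratum SD units; an IUGR hazard ratio for reaching full feeding; an arm effect of 1.3 SD or a hazard ratio of 3; exponential times; no censoring.

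**Growth, by formula.** Within-stratum variance is σ².

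- The true variance of the arm difference is σ²(1/10 + 1/10) = 0.2σ². The stratum effect is absent because each arm holds 5 infants of each kind.
- The variance the plain t-test estimates has expectation σ²[1 + 10(b/2)²/9] = σ²(1 + 0.278b²).
- The standard error is therefore inflated by about √(1 + 0.278b²): 1.03, 1.13 and 1.27 for b = 0.5, 1 and 1.5.
- Multiplying the critical value 2.101 (18 df) by these factors gives 2.17, 2.37 and 2.68. The corresponding two-sided tail areas are about 4.3%, 2.9% and 1.5%.

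**Growth, by simulation.** Plain t-test against a linear model with arm and stratum:

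| IUGR effect (SD) | Type I error, plain | Type I error, adjusted | Power, plain | Power, adjusted |
|---|---|---|---|---|
| 0 | 5.0% | about 5% | 78% | 78% |
| 0.5 | 4.2% | about 5% | 77% | 78% |
| 1 | 2.9% | about 5% | 70% | 78% |
| 1.5 | 1.4% | about 5% | 60% | 78% |

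The simulated error rates agree with the formula.

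**Time to full feeding, by simulation.** Log-rank test against log-rank stratified by IUGR; power at an arm hazard ratio of 3:

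| IUGR hazard ratio | Type I error, plain | Type I error, stratified | Power, plain | Power, stratified |
|---|---|---|---|---|
| 1 | 6.5% | about 6% | 61% | 56% |
| 0.5 | 5.3% | about 6% | 56% | 57% |
| 0.33 | 3.8% | about 6% | 47% | 56% |
| 0.25 | 2.9% | about 6% | 42% | 57% |

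A rerun of both tables with 200,000 trials per setting gave every figure within about one percentage point. At an arm hazard ratio of 3.5 the pattern is the same: 72%, 66%, 59% and 52% plain, against about 67% stratified.

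**The case against.** The strongest objection concerns the log-rank test. A reader might infer that both planned tests have a wrong, conservative error rate. For the log-rank test the calculations do not support that in general. Down to an IUGR hazard ratio of about 0.5 its type I error is not below 5%, and its power equals or exceeds that of the stratified test. With 20 infants both versions run slightly above 5%. This objection stands and limits the point for feeding time to a strong IUGR effect.

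Second, every size above rests on assumed effects. The Discussion says only that the condition may be present in IUGR infants and may slow feeding. A reader might infer that the article also expects IUGR to affect growth after randomization; it does not say so. At 0.5 SD the loss for growth is about one point of power. This stands too.

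Third, a reader might infer that the randomization-day weight, length and head circumference go unused. The Endpoints and Statistical analysis sections make the main growth comparison one between randomization and full feeding. That most naturally means change from randomization, so baseline probably enters the endpoint already and a constant size difference between strata would cancel. The stratum itself still does not enter.

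Fourth, covariates for secondary endpoints are often left to a statistical analysis plan, and calling the log-rank comparison univariate does not rule out a further adjusted one. This carries less weight, because the article does name the tests, and as named they do not use the randomization stratum. Any adjusted analysis would be an addition to what is written.

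Finally, the simulations use equal cells and no withdrawals, whereas the article speaks of approximate numbers and allows censoring. The figures are therefore indicative.

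**Conclusion.** The point holds as a mismatch between a stratified design and unstratified secondary analyses, with a conditional cost.

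- Growth: the plain t-test is conservative for any non-zero IUGR effect. The loss is about 1 point of power at 0.5 SD, 8 points at 1 SD (78 − 70) and 18 points at 1.5 SD (78 − 60).
- Time to full feeding: there is practically no loss at an IUGR hazard ratio of 0.5, about 9 points at 0.33 (56 − 47) and about 15 at 0.25 (57 − 42). If IUGR has no effect, the planned test is the better one by about 5 points (61 − 56).

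These sizes depend on the assumed IUGR and arm effects and on equal cells. A reader might infer that the trial's main conclusion is at risk. It is not: the primary CSOR test is paired within infant, and the power in Table 1 does not depend on this choice. Only secondary endpoints of a self-described explorative study are affected, and where the tests become conservative the risk is a missed effect, with no added false positives. The change is worth making because it costs little and these comparisons, at 10 per arm, have little power to spare.

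**What to change.** In Statistical analysis, replace the two by-arm specifications:

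- **Growth:** a linear model for each measure at full enteral feeding, with randomized arm, IUGR stratum and the randomization-day value of that measure. If normality fails, use a rank test stratified by IUGR (van Elteren) in place of Mann–Whitney.
- **Time to full enteral feeding:** a log-rank test stratified by IUGR, or a Cox model with arm and IUGR as covariates. Name one of them as the main analysis before outcome data are seen.
- Keep the unadjusted t-test and log-rank test as supportive analyses.

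The cost is a change of wording, 1 to 2 degrees of freedom in the growth model, and about 5 points of log-rank power if IUGR turns out to be unrelated to feeding time. No change to design, data collection or sample size is needed.
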